### Randomization and blinding

2.6

Using a random block allocation method (block sizes of 4 and 6), subjects were assigned in a 1:1 ratio to either the active or sham rTMS group. The sequence for randomization will be produced by an individual statistician who is not involved in the recruitment of patients or the assessment of outcomes, using SAS software (version 9.4; SAS Institute, Cary, North Carolina, United States). This serial number will be enclosed in a sequentially numbered, impervious to light, sealed envelope. Upon eligibility confirmation and consent, the researcher will open the next envelope in sequence and execute the assignment. Sequentially numbered, opaque, sealed envelopes will be opened only after participant enrollment and consent. The envelope will not be resealed. To assure compliance with the Blind Method, patients will be informed during preoperative consultations about potential sensations experienced during therapy, including tapping, pricking, warmth, or vibration. Patients will also be explicitly advised that the intensity of these sensations varies among individuals and should not be used as a basis for evaluating treatment efficacy. The stimulation devices are identical in appearance; the only difference lies in the placement angle of the coil during stimulation. The device is to be managed by independent researchers not participating in the study, and the screen is to remain off prior to treatment. Each participant will complete a questionnaire after the intervention to infer group assignment, with data reported and analyzed using the Bang blind index. All personnel involved in outcome assessment, data analysis, surgery, and the participants themselves will be blinded to group assignment. The outcome evaluators will undergo rigorous blinding training prior to the study commencement to familiarize themselves with operational processes and standards, thereby minimizing the impact of subjectivity on results.

### Unblinding

2.7

During the intervention phase, participants will undergo systematic evaluation to screen for potential rTMS-related complications or life-endangering symptoms. Prospective undesirable events include seizures, syncope, vagal reactions, headache, and auditory discomfort. The principal investigator may unblind the study only when complications requiring urgent medical intervention arise.

### Anesthesia management

2.8

Patients receive standard preoperative educational counseling and anesthesia consultation, including medical history review, explanation of the anesthesia plan, and disclosure of potential risks. They sign informed consent forms for anesthesia and the experimental procedure. Once in the operating room, peripheral venous access is established, and noninvasive blood pressure, electrocardiogram, and pulse oximetry are monitored. After a negative Allen’s test, radial artery cannulation will be performed under local anesthesia with lidocaine for arterial blood gas analysis and invasive blood pressure monitoring. Bispectral index (BIS) electrodes will be placed on the forehead for depth of anesthesia monitoring.

Anesthesia induction will be achieved via intravenous administration of propofol (1.5–2 mg/kg), sufentanil (0.1–0.5 μg/kg), and cisatracurium (0.15 mg/kg). A properly sized double-lumen endotracheal tube or bronchial blocker will be inserted via rapid sequence intubation. Initial mechanical ventilation parameters will be set as follows: tidal volume 6–8 mL/kg, respiratory rate 12 breaths/minute, FiO_2_ 1.0, maintaining end-tidal carbon dioxide pressure (PETCO_2_) within the range of 35–45 mmHg. Maintenance anesthesia employed a combined intravenous-inhalation technique: continuous propofol infusion at 4–6 mg/(kg⋅h), continuous remifentanil infusion at 8–10 μg/(kg⋅h), supplemented with 1% sevoflurane inhalation (targeting a brain-stem evoked potential BIS of 40–60). Vasopressors will be administered to maintain mean arterial pressure and heart rate within 20% of baseline values. Cisatracurium (0.05 mg/kg) will be given as needed on an intermittent basis.

Discontinue sevoflurane inhalation 30 min prior to the end of surgery.

All anesthetic agents will be discontinued upon completion of the procedure. The patient will be moved to the post-anesthesia care unit (PACU). Postoperative patient-controlled intravenous analgesia (PCIA) will be administered: Sufentanil 2 μg/kg + Ondansetron 0.2 mg/kg + Normal Saline to a total volume of 100 ml; baseline infusion rate 2 ml/h, PCA bolus dose 0.5 ml, with a 15-min lockout interval. Extubation criteria: when the patient can respond to verbal commands, regain muscle strength, and demonstrate satisfactory respiratory parameters. Patients with a Steward score > 4 can be transferred to the ward. Rescue analgesia (intravenous tramadol 50 mg) will be administered if the NRS pain score exceeds 4.

### Study intervention

2.9

During the morning of the day before surgery, researchers will identify prospective participants based on the surgical schedule. Interventions will occur at two time points (Table 1): (1) First intervention: Afternoon before surgery in the ward. (2) Second intervention: 30 min before surgery on the operation day. The Mag TD rTMS device (Yiruide Medical Equipment, Wuhan, China) with its figure-of-eight coil will be used. We chose the left M1 region as the stimulation target because the left hemisphere is the dominant hemisphere for most people, and its neuroplasticity and regulatory potential may be stronger. A study published in 2024 confirmed that rTMS targeting the left M1 can selectively increase the concentration of β-endorphin in plasma. β-endorphin is one of the strongest “natural painkillers” in the human body. This provides direct neurochemical evidence for left M1 stimulation (24). Therefore, in research, to unify standards and reduce variables, the left M1 has become the most commonly used target with the most comprehensive research data (28). For the group receiving effective rTMS, stimulation of the M1 region will be performed by an independent investigator not involved in this study (as shown in Figure 2). M1 localization will utilize the international 10–20 electroencephalography system (29). This location is situated approximately 5 cm posterior-lateral and 6 cm anterior to the vertex of the head, and can be confirmed using a positioning cap. Single-pulse transcranial magnetic stimulation is employed for precise localization to determine the optimal stimulation point capable of eliciting the most stable motor-evoked potential (MEP) in the contralateral flexor digitorum superficialis muscle. As clinical studies on rTMS for APSP are limited, stimulation parameters are based on preclinical evidence. The stimulation frequency will be 10 Hz, intensity at 90% of the resting motor threshold (RMT). Each train will last 10 s, followed by a 20-s inter-train interval, for 30 trains totaling 3,000 pulses. RMT is a defined by the minimum stimulus intensity (expressed as a percentage of maximum output) required to elicit a MEP of >50 μV in at least five out of 10 consecutive trials while the target muscle is in a relaxed state (30). For the sham rTMS group, the device and coil placement will be identical, but the coil will be tilted 90° away from the scalp. This produces similar auditory and somatosensory cues (sound, vibration) without delivering effective magnetic stimulation to the cortex, serving as a placebo control (31). Professionally trained researchers will strictly follow operating procedures and closely monitor participants’ responses throughout the intervention to make sure no adverse reactions occur. Should participants report intolerable discomfort, the stimulus will be immediately discontinued. A limitation of this approach is that pseudo-stimulation achieved through 90° coil tilt may not fully match scalp sensations, and depending on the geometry, it may still induce partial cortical stimulation.

**TABLE 1 T1:** The study schedule for enrollment, treatments, outcome measurements, and data collection.

Study period									
Time point	Enrollment		Post-randomization						
	Pre-2	Pre-1	30 min before surgery	2 h after surgery (T1)	6 h after surgery (T2)	12 h after surgery (T3)	24 h after surgery (T4)	48 h after surgery (T5)	90 days after surgery (T6)
Enrollment									
Inclusion criteria	✓	–	–	–	–	–	–	–	–
Exclusion criteria	✓	–	–	–	–	–	–	–	–
Informed consent	✓	–	–	–	–	–	–	–	–
Randomization	–	✓	–	–	–	–	–	–	–
Interventions									
Active rTMS group	–	✓	✓	–	–	–	–	–	–
Sham rTMS group	–	✓	✓	–	–	–	–	–	–
Outcome measurement									
Postoperative resting pain score (NRS)	–	–	–	✓	✓	✓	✓	✓	✓
Postoperative movement pain scores (NRS)	–	–	–	✓	✓	✓	✓	✓	✓
Postoperative recovery quality index (QoR-15)	–	–	–	–	–	–	✓	✓	–
Remedial analgesic dosage (MME) in the first 48 h postoperatively	–	–	–	–	–	–	–	✓	–
Incidence of moderate to severe pain at 24 h postoperatively	–	–	–	–	–	–	✓	–	–
Adverse events	–	–	–	✓	✓	✓	✓	✓	✓

According to SPIRIT 2013 statement: defining standard protocol items for clinical trials. Pre-2, 2 days prior to the surgery; pre-1, the day before the surgery; MME, morphine mg equivalent; QoR-15, Quality of Recovery-15.

**FIGURE 2 F2:**
[figure not shown]
The magnetic stimulation coil was positioned over the M1 location. Transcranial magnetic stimulation.

### Outcomes

2.10

#### Primary outcome

2.10.1

The primary outcome is the incidence of moderate-to-severe pain at 24 h postoperatively. APSP is common after VATS, often peaking within 24–48 h (32). Pain can inhibit breathing leading to atelectasis and impair postoperative mobility and physiotherapy (33). Pain intensity will be recorded using the Numerical Rating Scale (NRS) (34). An NRS score ≥ 4 is defined as moderate-to-severe pain (35). The primary outcome measure will be the NRS score for the most severe pain experienced within 24 h, recorded prior to any rescue analgesic administration.

#### Secondary outcomes

2.10.2

The postoperative period is defined as starting from the time of PACU admission.

(1).Time to first PCIA demand (from surgery end to first effective PCA button press with drug delivery).(2).Resting pain scores (NRS) at 2 h (T1), 6 h (T2), 12 h (T3), 24 h (T4), 48 h (T5), and 90 days (T6) postoperatively. Resting pain is assessed while the patient is lying quietly.(3).Movement pain scores (NRS) at T1–T6 postoperatively. Movement pain is assessed during turning or coughing.(4).PACU length of stay (hours from PACU admission to discharge).(5).Area under the curve (AUC) for resting pain scores from T1 to T5 (0–48 h), calculated using the trapezoidal rule, to quantify total pain burden.(6).AUC for movement pain scores from T1 to T5 (0–48 h), calculated using the trapezoidal rule.(7).Quality of Recovery assessed by QoR-15 score at 24 h (T4) and 48 h (T5) postoperatively.(8).Extubation time (minutes from cessation of all maintenance anesthetics to safe removal of the endotracheal tube). The decision to extubate, made by a blinded anesthesiologist, will be based on standard clinical criteria.(9).Record the dosage of rescue analgesics administered within 48 h postoperatively, expressed in milligram equivalents of oral morphine (MME). Rescue analgesia is administered according to the protocol if the patient’s resting pain numerical rating scale (NRS) score is ≥4 within 48 h postoperatively. For standardized comparison, all opioid medications are converted to milligram equivalents of oral morphine based on the American Academy of Pain Medicine guidelines (36).

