### Statistical analysis

2.14

Analysis will follow the intention-to-treat (ITT) principle using SPSS 27.0, with graphs created in GraphPad Prism 8.0. The Kolmogorov-Smirnov test will check normality, and Levene’s test will evaluate variance homogeneity. Data will be presented as mean ± standard deviation for normal distributions and median with interquartile range for non-normal distributions.

Continuous variables will be assessed with the *t*-test or Mann-Whitney U test, depending on distribution. Categorical variables, including the primary outcome, will be examined using chi-square tests or Fisher’s exact test, with differences shown as relative risk and 95% CI. Comparisons of primary outcomes used generalized estimating equations (GEE). The interaction between treatment and time was first assessed. If this interaction was statistically significant, Bonferroni-corrected multiple comparisons were performed to assess differences between groups at each individual time point. If not, the primary treatment effect was then assessed at each time point without applying the Bonferroni correction. For other replicated measurement data, GEE were similarly employed for analysis. Multivariate analysis will use linear or logistic regression models based on the outcome type. Missing data will be addressed with multiple imputation, and a per-protocol analysis will be included for sensitivity. Benjamini-Hochberg correction for secondary outcomes. A significance level of α = 0.05 will be applied, with *p* < 0.05 deemed significant.

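### Time to first PCIA demand can be right-censored, but the listed methods include no time-to-event analysis and set no rule for patients who never press

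*Protocol article*

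**What the plan says.** Section 2.10.2 (Secondary outcomes), item 1, defines the outcome as "Time to first PCIA demand (from surgery end to first effective PCA button press with drug delivery". The abstract also lists it. Neither place gives an end of observation, or a value for a patient who never presses.

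Section 2.8 (Anesthesia management) gives every patient PCIA made up with "Normal Saline to a total volume of 100 ml" and a basal rate of 2 ml/h. It also provides tramadol rescue triggered by a pain score, so pain can be treated without a press.

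Section 2.14 (Statistical analysis) assigns methods by type of variable:

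- Continuous outcomes are compared by t-test or by "Mann-Whitney U test, depending on distribution".
- Categorical outcomes go to chi-square or Fisher's exact test, and repeated measures to GEE.
- For modelling, the choice is closed: "Multivariate analysis will use linear or logistic regression models based on the outcome type".
- For absent values, one general rule covers every outcome: "Missing data will be addressed with multiple imputation".

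No Kaplan-Meier, log-rank or Cox method appears anywhere in the article.

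**The concern.** This is a time to event. A patient who reaches the end of PCIA without pressing has no event time; all that is known is that it lies beyond the end of observation. The listed methods have no place for that information. A duration fits only the class of continuous variables, and the regression sentence admits only linear or logistic models. The imputation rule makes no exception for an event that did not occur.

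Two natural ways of applying these rules would do harm. Leaving never-pressers out conditions on something that happens after randomisation, which sits badly with the ITT principle that section 2.14 declares. Treating the absent time as missing and imputing it turns an event that had not occurred by the end into one that occurred but went unrecorded. If active stimulation delays the first press, both remove part of the effect that the outcome is meant to show.

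**Working it through.** **Inputs from the article.** Reservoir 100 ml and basal rate 2 ml/h (section 2.8); 260 patients, 1:1, 10% dropout (sections 2.6 and 2.13). The article states no figure for this outcome, so there is none to reproduce. Its one sample-size figure, 103 per group for 70% against 50%, does reproduce with the continuity-corrected two-proportion formula (93 without the correction), and nothing below touches it.

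**Can the outcome be censored?** Pump duration without a bolus = 100 / 2 = 50 h. A patient can therefore pass 48 h with the pump running and no press recorded.

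**Assumptions, none of them in the article.** Exponential times, observation to 48 h, a share p of sham patients who never press, hazard ratio (HR) 0.67, two-sided 0.05 before the Benjamini-Hochberg correction. Then:

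- sham hazard = −ln(p)/48, and active hazard = 0.67 × sham hazard;
- share never pressing on active = p^0.67; for example 0.30^0.67 = 0.446.

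**Simulated power with all 130 per arm (260/2):**

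| Never press, sham | Never press, active | Dropped, Mann-Whitney | Imputed, t-test | Kept at 48 h, Mann-Whitney | Log-rank |
|---|---|---|---|---|---|
| 2% | 7% | 58% | not run | 80% | 89% |
| 5% | 13% | 43% | 44% | 78% | 86% |
| 10% | 21% | 31% | 33% | 78% | 84% |
| 20% | 34% | 17% | 17% | 74% | 78% |
| 30% | 45% | 10% | 10% | 70% | 72% |
| 40% | 54% | 8% | 8% | 64% | 66% |

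**With 117 per arm (260 × 0.9 / 2):**

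- At 2% to 10% never-pressers on sham, power is about 52% falling to 26% when they are dropped, 72–74% with the 48 h ceiling, and 84% falling to 79% with log-rank.
- At 30% against 45% never pressing (HR = ln 0.45 / ln 0.30 = 0.66), the three figures are about 11%, 67% and 69%.

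**What imputation does to the estimate.** Imputation was by arm from a normal model, combined with Rubin's rules. For 5% to 40% never-pressers on sham, about 99.5% to 97% of the imputed times fell below 48 h, although every true time lay beyond it. The true difference in restricted mean time to 48 h is the difference between arms in (1 − e^(−48λ))/λ, where λ is the arm's hazard:

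| Never press, sham | Estimated delay after imputation | True restricted-mean difference |
|---|---|---|
| 5% | 2.9 h | 5.5 h |
| 10% | 2.6 h | 5.7 h |
| 20% | 1.9 h | 5.5 h |
| 30% | 1.5 h | 5.0 h |
| 40% | 1.1 h | 4.4 h |

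**Type I error.** With HR = 1, dropping, the 48 h ceiling and log-rank all rejected in 4.2% to 5.7% of simulated trials. Imputation was not simulated under no effect.

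**The case against.** The strongest reply is that the article never says what a reader might infer, namely that never-pressers are dropped or given invented times. Section 2.14 does not assign this outcome to a test by name, does not call the absence of a press missing data, and declares ITT, which argues against silent exclusion. That reply stands: exclusion and imputation are possible results of the listed rules, not stated ones.

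A third reading also fits the listed methods: give never-pressers the 48 h value and use Mann-Whitney. It is nearly adequate, costing about 1 to 9 points of power against log-rank with 130 per arm and about 2 to 11 with 117. The large gaps in the table therefore come from discarding or imputing patients, not from the choice of rank test. But the article does not state this rule, so the choice among the three could be made after the data are seen.

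It may also be said that an analysis plan, not shown here, would settle the matter. Silence alone would be no finding. Here, however, the article states a set of methods by variable type, a closed choice of regression models and an unqualified imputation rule, and that set does not suit one of its own outcomes.

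Three further inferences are not supported:

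- Never-pressers need not be the best responders. No press may also reflect the basal infusion, tramadol rescue, an ICU stay or withdrawal.
- The clock need not move. Section 2.10.2 starts the postoperative period in general at PACU admission, but gives this outcome its own explicit origin, surgery end, which governs and applies alike in both arms.
- Inflated false positives are not shown in the set-ups checked.

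**Conclusion.** The point holds as a mismatch between one secondary outcome and the methods listed for it. The outcome can be right-censored by design, and the article gives no end of observation, no rule for patients without an event, and no time-to-event method.

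The size depends on how never-pressers would be handled and how many there are, and the article gives neither. If they were excluded or imputed, power would fall by roughly a third or more even at 2% on sham (84% to 52% with 117 per arm) and to about 11% at 30%, and the estimated delay would shrink to between about half and a quarter of its true restricted-mean value. If they were kept at a 48 h ceiling, little would be lost. These figures rest on exponential times, a hazard ratio of about 0.67 and a common 48 h horizon.

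The harm is dilution and lost power on a secondary outcome. The primary outcome and sample size are not affected. The change is worth making, but the trial's main conclusion does not hang on it.

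**What to change.** Add to section 2.14, and carry into the analysis plan, that for time to first PCIA demand:

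- a patient who completes observation without a press is a censored observation, not missing data, and no event time is imputed;
- observation ends at 48 h, or at the end of PCIA if earlier;
- all randomised patients are analysed, with Kaplan-Meier curves and a log-rank test or Cox hazard ratio, or with the difference in restricted mean time to 48 h;
- withdrawal before the end of observation is handled separately from reaching the end without a press.

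The origin may stay at surgery end as defined. The data needed are the time of the first effective press and the time PCIA ended. The cost is one or two sentences before database lock, with no change to sample size, visits or the Benjamini-Hochberg family.

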### Adverse events and safety

2.11

All adverse events (AEs), regardless of relationship to rTMS, will be documented in detail, including time of onset, severity, relationship to intervention, actions taken, and outcome. SAEs must be reported to the Ethics Committee and principal investigator within 24 h, and participation in the study will be terminated. The study has a low risk of bias. An independent Data Monitoring Committee (DMC) will oversee the data, especially if adverse events occur. To address potential futility, the DMC will periodically review safety and efficacy data and perform an interim analysis when about 50% of data is collected. The O’Brien-Fleming alpha allocation function was employed, with the interim significance threshold set at *p* < 0.003. The interim analysis was conducted solely for safety and futility assessments and did not involve early termination for efficacy. If a negative reaction is suspected during the intervention, the study will be stopped immediately, and unblinding will occur quickly to ensure participant safety.

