### Discontinuation criteria

2.5

(1).Intraoperative conversion to thoracotomy or extended surgical scope (e.g., pneumonectomy, pleuropneumonectomy).(2).Postoperative ICU stay exceeding 24 h, preventing effective assessment.(3).Patient or family requests withdrawal at any stage.(4).A serious adverse event occurred, leading the investigator to determine that the intervention must be terminated.

The participants have the privilege to drop out of the study at any time for any reason, and this will not affect their routine medical care. The research team will ensure appropriate care continues to be provided and will document in detail the reasons for withdrawing from the study. Additionally, the investigator may discontinue a participant’s involvement in case of severe organ dysfunction, protocol non-compliance, or occurrence of serious adverse events (SAEs).

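### Sections 2.7 and 2.11 contradict each other on whether a suspected but non-urgent reaction to stimulation leads to unblinding

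*Protocol article*

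**What the plan says.** Four sections of the protocol article deal with a participant who reacts badly to stimulation.

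- Section 2.7 (Unblinding) restricts code-breaks: "The principal investigator may unblind the study only when complications requiring urgent medical intervention arise". The sentence before it lists what is foreseen: "Prospective undesirable events include seizures, syncope, vagal reactions, headache, and auditory discomfort".
- Section 2.11 (Adverse events and safety) ends with: "If a negative reaction is suspected during the intervention, the study will be stopped immediately, and unblinding will occur quickly to ensure participant safety".
- Section 2.9 (Study intervention) says: "Should participants report intolerable discomfort, the stimulus will be immediately discontinued".
- Section 2.5 (Discontinuation criteria) includes: "A serious adverse event occurred, leading the investigator to determine that the intervention must be terminated".

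On blinding itself, section 2.6 states: "All personnel involved in outcome assessment, data analysis, surgery, and the participants themselves will be blinded to group assignment". It also plans a questionnaire after the intervention in which each participant guesses the allocation, analysed with the Bang blinding index.

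**The concern.** Section 2.7 sets a narrow condition for breaking the code. Section 2.11 sets a wide one: suspicion alone, with no severity threshold. Someone at the bedside with a participant who reports a headache during stimulation cannot obey both.

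At stake is the blind on which the sham comparison rests. Under section 2.10.1 the primary outcome is the participant's own rating of worst pain within 24 h, classed as moderate-to-severe at NRS 4 or above. A self-rating can be shifted by knowing which treatment was given. Both stimulation sessions take place before surgery (section 2.9 and Table 1), so any code-break made during a session comes before every pain score.

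**Working it through.** No figure in the plan decides this point, so the check is a comparison of the text.

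**Step 1. The rules side by side.**

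| Section | Trigger | What stops | Code-break | Who decides |
|---|---|---|---|---|
| 2.5 | Serious adverse event, on the investigator's judgement | That participant's intervention | Not mentioned | Investigator |
| 2.7 | Complication needing urgent treatment | Not mentioned | Permitted, and only then | Principal investigator |
| 2.9 | Discomfort the participant cannot tolerate | The stimulus | Not mentioned | Not named |
| 2.11 | Suspicion of a negative reaction, no severity given | *The study* | Ordered, and quickly | Not named |

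**Step 2. Apply 2.7 and 2.11 to the reactions that 2.7 lists.**

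- *An urgent complication, for example a seizure needing immediate treatment.* Section 2.7 permits unblinding and 2.11 orders it. There is no conflict.
- *A headache or auditory discomfort that needs no urgent treatment.* Section 2.11 orders unblinding as soon as a negative reaction is suspected; 2.7 rules it out. Both cannot be followed.

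The contradiction is therefore confined to non-urgent reactions, but these are reactions the plan itself expects.

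**Step 3. Check 2.9 and 2.5.** Section 2.9 stops the stimulus and is silent on the code. It can be followed together with 2.7: stop stimulating, keep the blind. Section 2.5 is also silent on the code. Neither adds a further contradiction on unblinding. Both matter because they describe a stop for one participant, whereas 2.11 speaks of the study.

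**Step 4. Timing.** Table 1 places the interventions on the day before surgery and 30 min before surgery, and the first pain score at 2 h after surgery. A code-break during either session precedes the whole 24 h window of the primary outcome. If the participant were told the allocation before completing the section 2.6 questionnaire, the Bang index would be distorted as well.

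**Step 5. Can the loss be sized by arm?** With 1:1 allocation, the active arm's share of code-breaks is a / (a + s), where a and s are the reaction rates under active and sham stimulation. The documents give neither. Purely as assumptions:

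- a = s = 5%: 0.05 / 0.10 = 50%
- a = 5%, s = 2%: 0.05 / 0.07 = 71%
- a = 2%, s = 5%: 0.02 / 0.07 = 29%

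The answer is set entirely by the assumed rates, so neither size nor direction can be derived from the plan.

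**The case against.** The best defence is that the last sentence of 2.11 is loosely worded and was meant for serious reactions in one participant, in which case it agrees with 2.7. Much of that stands as an account of intent. It does not remove the conflict, because the sentence names no severity and is triggered by suspicion.

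A reader might infer more than the documents support, in four ways.

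- *That one suspected reaction halts the trial.* The words of 2.11 can be read so, but the sentence concerns events during the intervention and the safety of the participant. The same section ends only individual participation after a serious adverse event. Stopping the trial for a lesser event would be odd, so the participant's session is the likelier meaning. What remains is an ambiguity to remove.
- *That blinding is lost mainly in the active arm.* Sham stimulation is described thus: "This produces similar auditory and somatosensory cues (sound, vibration) without delivering effective magnetic stimulation to the cortex". Auditory discomfort could therefore arise in either arm. The authors also concede that the sham "may not fully match scalp sensations, and depending on the geometry, it may still induce partial cortical stimulation". A sensory mismatch makes some imbalance plausible; partial stimulation under sham would tend to reduce it. Neither is quantified.
- *That the 24 h score would be biased.* This needs the allocation to reach the participant or the assessor. Section 2.6 says both are blinded, and no section says that either is told after a code-break. A code-break known only to the treating team need not affect the score.
- *That staff have no rule at all during stimulation.* Sections 2.9 and 2.11 can both be read as stopping stimulation at once. The gap concerns the code and the scope of the stop.

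It is also fair to say that who is told after a code-break is operational detail that an article may leave to the full protocol. Its absence is not the finding. The finding is that two stated rules disagree.

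**Conclusion.** This is an internal contradiction, established from the text alone. Sections 2.7 and 2.11 give opposite instructions on unblinding for a suspected reaction that is not urgent, and the same instruction for an urgent one. The scope of the stop in 2.11 is ambiguous as well.

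The consequence is conditional. If 2.11 is followed as written, and if the allocation then becomes known to participants or assessors, blinding is compromised before a self-reported primary outcome. The loss may be unequal between arms, but its size and direction cannot be calculated. No sample-size or analysis figure in the plan changes. The point deserves correction because the conflict touches both safety conduct and the blind, and section 2.1 reports that recruitment is already underway.

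**What to change.** Reconcile sections 2.5, 2.7, 2.9 and 2.11 into one rule that:

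- treats stopping stimulation and breaking the code as separate decisions, each with one stated trigger and a named decision maker;
- says whether the stop in 2.11 applies to the participant's session or to the trial;
- leaves the clinical triggers to the sponsor and the data monitoring committee (this review takes no position on which existing rule is right).

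In the same amendment, state that a code-break is disclosed only to those who need it for the participant's care, that outcome assessors and analysts stay blinded, and that the 24 h NRS score is still collected and analysed as randomised. The last item follows from the intention-to-treat principle already given in section 2.14.

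The cost is a wording amendment and a short instruction to the site, with no added patients or procedures.
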